### Study design overview

This mixed-methods study will involve two stages. Stage One will undertake an Australia-wide audit of a representative sample of RUM bins. The objectives of this stage are:To quantitatively describe the amount and types of medicines returned to pharmacies using a statistically valid sample of returned RUM bins from all states and territories of Australia; andTo identify the proportion of waste that is PBS-subsidised and to extrapolate the value of ‘wastage’ to the PBS.

In Stage Two a two-step general population survey will be conducted. Step One will utilise an online household survey with a general population sample. Step Two will invite a sub-set of survey respondents from Step One who take five or more medicines, to participate in a telephone interview. The objectives of Stage Two are:To assess general population awareness of: the NatRUM scheme; practices for the disposal of unwanted medicines; and the risks of accumulating medicines;To identify general population practices for household disposal of unwanted medicines in the previous 12 months;To quantitatively describe the volume of unwanted or expired medicines stored in the households of a sub-set of the general population with higher medication burden; andTo qualitatively explore the storage and disposal practices of a sub-set of the general population with higher medication burden.

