	Medicines characteristics once dispensed
	Year dispensed^a^
	Quantity dispensed^a^
	Quantity returned^a^
	Evidence of medicine use^a^
	Proportion of dispensed quantity unused^a, b^
	Medicine unlabelled
	Category of medicine dispensing (e.g. concession or general)^a^
	Dose administration aids (DAA)
	Type of DAA
	Proportion of medicines unused in DAA

*PBS = Pharmaceutical Benefits Scheme; S2 = Pharmacy medicine; S3 = Pharmacist-only-medicine; S4 = Prescription medicine; S8 = Controlled medicine*

^a^
*These variables extend the evidence base of data collected during the 2013 audit*

^b^
*Only medicines packaged as foil strips/blisters will be counted and assumptions used in the New Zealand DUMP project audit* [22] *will be applied to documentation of quantity of returned inhalers, creams, liquids*

Audit training tools, including a data collection protocol and quality assurance procedure, and Occupational Health and Safety (OH&S) Standard Operating Procedure (SOP) were developed in consultation with incineration plant managers, personnel from Griffith University OH&S and NatRUM Ltd. (all training tools and protocols are available from correspondence author on request).

Data collection will be conducted at each of the three incineration sites by research assistants, working in pairs (one person inspects and counts whilst the second enters the information into the database), under the supervision of the project Data Collector Manager, (a registered pharmacist). An additional research assistant will be available at each site to act in a quality control role and to provide cover for breaks and/or absences such as unexpected illness. Data collectors will be trained at each site to safely audit a RUM bin and to enter data into the Access® database. Training will include familiarisation with the specific auditing equipment including protective clothing (gloves, safety glasses, dust masks, coveralls), and tools (tongs, tweezers, scales), and a demonstration of how to safely open and assess the contents of a RUM bin. Training will also emphasise the importance of the confidential nature of bin contents including any pharmacy, prescriber and patient information. A representative from Griffith University OH&S will be present for this training.

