#### Bin and contents inspection

Each RUM bin will be visually inspected prior to opening to record the source of the bin (state/territory and wholesaler returning the bin), container weight and bin identification number. On opening the bin, the contents are spread over a table and visually inspected for any signs of hazardous materials. If inappropriate items are found, the bin is to be immediately resealed and sent for incineration. RUM bins will be excluded from further assessment if they: are less than 50% full; or contain a high proportion of general waste; or contain more than 50% loose tablets (not in an identifiable bottle/packet or blister/strip); or contain hazardous items such as broken glass, biological waste, unknown liquid or powder waste.

Once it is decided that a bin is suitable for auditing, details of each discarded medicine will be recorded in the database. Information recorded includes the name of the medicine (brand or generic), strength and pack size. The expiry date, schedule, if there is a dispensing label present, dispensing category and year dispensed is then recorded, together with the quantity returned. For items that are a unit dose (i.e. tablets, capsules, nebules, prefilled syringes, etc.), the exact number of units returned is counted. For liquids, the percentage returned is estimated (empty = 0%; 1–25% = 25%; 25–50% = 50%; 50–75% = 75%; and 75–100% = 100%) and creams, gels and ointments are weighed to assess volume remaining. The amount remaining in aerosols is recorded from the dose indicator or estimated by placing the device/canister in water to determine whether it is full (quickly sinks), used (slowly sinks) or empty (floats). Loose tablets and capsules (i.e. those not in bottles or blister packs) and products that are unidentifiable (e.g. from another country or not in original packaging) will be excluded. Volumes of complementary and/or alternative medicines returned will be estimated rather than counted (0–25%, 26–50%, 51–75% or 76–100% full).

If dose administration aids are present, the type (e.g. dosette, blister or sachet pack) is to be recorded and proportion remaining estimated (e.g. 0%–25%, 26%–50%, 51%–75%, and 76%–100% full).

When an item is identified as a Schedule 8 (controlled) medicine, this will be recorded specifically in the database, together with any evidence of destruction (i.e. cut and empty foil strip or an empty bottle).

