#### Data analysis

For data collection purposes, *trade product pack terms* are used, allowing data collection personnel to search and select on branded or generic names of products, for example:Panadeine Caplet® (codeine phosphate hemihydrate 8 mg + paracetamol 500 mg) tablet: film-coated, 12 tablets.

Use of the AMT allows linkage between trade product pack terms with other formal definitions such as the *medicinal product pack term*:paracetamol 500 mg + codeine phosphate hemihydrate 8 mg tablet, 12 tablets; and *the medicinal product term*:paracetamol + codeine.

Following data collection the trade product pack terms will be matched with both the medicinal product pack and medicinal product terms (using the SNOMED CT-AU v1.7 Common Release). AMT is also compatible with PBS data and hence the PBS dataset will be merged, along with the Anatomical Therapeutic Chemical (ATC) classification system number, into the bin audit database. This allows PBS items to be matched with a price (Manufacturer’s ‘Ex-Manufacturer Price’ for a manufacturer’s pack).

Automated matching will not be possible for manually entered items (where no trade product pack listing was available at data entry), requiring manual matching in some instances. Following data matching, audit data will be cleaned in preparation for visualisation and descriptive data analyses. Using a number of assumptions an extrapolated value of ‘wastage’ to the PBS will be estimated. This estimate is sensitive to the definition of waste, such as whether only unopened packs are counted, whether products were expired at the time of counting (but not necessarily at the time of disposal), and if a dispensing label was visible. Four assumptions will be tested and presented alongside the main results: i) dispensed, unopened, not expired; ii) dispensed, unopened, expired and not expired; iii) dispensed, opened and unopened, and not expired; and iv) dispensed, opened and unopened, expired and not expired.

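### The fill scales for complementary medicines and dose administration aids have no empty class, so an empty container cannot be told apart from one up to a quarter full

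*Protocol article*

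**What the plan says.** All the grading rules are in the Protocol article, Methods, Stage one, Bin and contents inspection.

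- Complementary and alternative products: "Volumes of complementary and/or alternative medicines returned will be estimated rather than counted (0–25%, 26–50%, 51–75% or 76–100% full".
- Dose administration aids: "proportion remaining estimated (e.g. 0%–25%, 26%–50%, 51%–75%, and 76%–100% full". The bands are introduced as an example.
- Liquids: "For liquids, the percentage returned is estimated (empty = 0%; 1–25% = 25%; 25–50% = 50%; 50–75% = 75%; and 75–100% = 100". Empty has its own class, and every other band is converted to its upper limit.
- Aerosols without a usable dose indicator are put in water to "determine whether it is full (quickly sinks), used (slowly sinks) or empty (floats".
- Unit-dose items are counted exactly, so a count of zero is possible.

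The first Stage One objective (Study design overview) is "To quantitatively describe the amount and types of medicines returned to pharmacies". Table 2 (Data collection and training) lists "Proportion of medicines unused in DAA" among the audit variables. The Stage One Data analysis section says that "audit data will be cleaned in preparation for visualisation and descriptive data analyses". It gives no rule for converting the bands of these two groups into quantities.

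**The concern.** The audit separates nothing left from something left for liquids, aerosols and counted items, but not for complementary products or dose administration aids. For an aid, whether it is finished or still holds doses is the basic fact behind the Table 2 variable on the unused proportion. For complementary products, the same fact decides whether an entry describes returned medicine or only packaging.

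The distinction has to be made when the data are entered, because the Background says that collected medicines are incinerated. A later analysis cannot split the band. The article also does not say whether an empty complementary-medicine container is to be entered at all. With about 15 pairs of collectors (Limitations), pairs could handle this differently.

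**Working it through.** The documents give no figure to reproduce here, so the check has two parts: comparing the scales, and asking what the lowest band does under each possible score.

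**Scales side by side**

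| Group | Separate empty class? | Numeric value stated for the bands? |
|---|---|---|
| Unit doses | Yes, a count can be 0 | Exact count |
| Liquids | Yes, 0% | Yes, the upper limit of each band |
| Aerosols | Yes | Dose indicator, or three states |
| Complementary medicines | No, the lowest band starts at 0 | None |
| Dose administration aids (example bands) | No, the lowest band starts at 0 | None |

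Footnote b to Table 2 borrows quantity assumptions from the New Zealand audit for inhalers, creams and liquids. It does not name complementary medicines or aids.

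**Effect of the score given to the lowest band**

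Assumptions, which are mine: a share q of the containers in the lowest band is empty, and the rest are spread uniformly over 0–25%, with mean 12.5%. Then

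- true mean fill in the band = 12.5 × (1 − q)
- bias = score − 12.5 × (1 − q), in percentage points of a full container

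| q (assumed) | True mean | Lower limit (0) | Midpoint (12.5) | Upper limit (25) |
|---|---|---|---|---|
| 0 | 12.5 | −12.5 | 0 | +12.5 |
| 0.25 | 9.4 | −9.4 | +3.1 | +15.6 |
| 0.5 | 6.25 | −6.25 | +6.25 | +18.75 |
| 1 | 0 | 0 | +12.5 | +25 |

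For a single empty container the error equals the score: 0, 12.5 or 25 points. Only the lower limit is right for empties, and it sets every part-full container in the band to zero. If only class frequencies are reported, no score is used and the table does not apply. The number of empties is then still unknown.

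**What a separate empty class changes**

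Empties then score 0 exactly, which removes q × score from the bias. At q = 0.5 with upper-limit scoring, this removes 0.5 × 25 = 12.5 points, so the bias falls from 18.75 to 6.25. With midpoint scoring it removes 0.5 × 12.5 = 6.25 points and leaves 0. With lower-limit scoring nothing changes.

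**Comparison with liquids**

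The stated liquids rule takes the upper limit. With contents uniform within a band, it rounds each non-empty band up by 25/2 = 12.5 points on average.

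**The case against.** The strongest objection concerns a stronger reading. A reader might infer that empty containers are recorded as part-full, so that the amount returned is overstated for these two groups. The documents do not support that. The lowest band includes zero, so an empty container is classified correctly. No quantity is attached to any of these bands, and the planned analysis is descriptive. Overstatement needs midpoint or upper-limit scoring, and the article specifies neither for these groups. This part of the objection stands in full.

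Other points also stand:

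- Liquids are no model of unbiased measurement, because their non-empty bands are all rounded up. Borrowing their empty class would not by itself make amounts comparable across types.
- No analysis is described that counts complementary-medicine containers or aids still holding medicine, so an overcount of such containers cannot be claimed.
- The PBS wastage estimate rests on dispensed items matched to a price. Nothing shows these bands entering it.
- A reader might also object that the top band merges full with started packs. The article says that the tools record whether a pack was opened, and Table 2 lists evidence of use. It does not say whether these items cover the two groups, so a loss at that end is not established.
- The bands for aids are only an example, and a fuller data collection protocol exists that is not shown. That half of the point is weaker.

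The objection does not remove the scale itself. For complementary medicines the bands are stated outright, not as an example, and they cannot separate nothing returned from something returned. The same section makes that separation for other forms.

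**Conclusion.** The point holds as a minor loss of information and an inconsistency between scales. For complementary medicines, and for aids if the example bands are used, an empty container and one up to a quarter full get the same entry, and the difference cannot be recovered after incineration.

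If the bands are converted to quantities, the error within the lowest band can lie anywhere from −12.5 to +25 percentage points of a full container. Where it falls depends on the score chosen and on the share of empties, and the range assumes uniform fill among the non-empty containers. The documents give neither input, so the direction and size of a bias are not established. With class frequencies alone there is no numeric bias, but packaging cannot be separated from returned medicine. The change is worth making because the loss is permanent and the remedy is small.

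**What to change.** Before the audit starts, add an empty (0%) class to the lists for complementary medicines and dose administration aids, and relabel the lowest band 1–25%. The three upper bands can stay as they are. State in the data collection protocol that empty containers are entered in the new class, and report them separately from the amount returned. If the bands will be converted to quantities, state the score for each band, since the new class does not settle that. It also does not align these groups with liquids, whose bands are scored at their upper limit.

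The cost is one extra data-entry option in each list and a line in the data collection protocol. The database has already been piloted with three bins and loaded onto the laptops, so the change must be made on every machine and covered in collector training.

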#### Data collection and training

Data collection tools and protocols developed specifically for the 2013 NatRUM audit were reviewed and refined to ensure that the audit will build on, and extend, the evidence base; e.g. whether medicines have been used (opened or full pack) and calculating the proportion of medicine that is returned (compared with 2013 where all medicine packs were treated as unopened and 100% contents were assumed) [20]. Additional variables were identified from a similar audit in New Zealand (DUMP project [22]) and in consultation with the NatRUM Ltd. Board. Table 2 outlines the variables, to be included in the audit. A purpose-built database has been developed in Microsoft Access®. We used Australian Medicines Terminology (AMT) - a subset of the SNOMED CT-AU clinical terminology, supported by the Australian Digital Health Agency (http://www.digitalhealth.gov.au/get-started-with-digital-health/what-is-digital-health/clinical-terminology remove extra line here and rejoin sentence). This national terminology unambiguously identifies branded and generic medicines commonly used in Australia. It includes a list of most prescription and OTC medicines and complementary products sold in Australian pharmacies, allowing generic and/or trade names to be easily searched and data such as form, strength and original quantity to be easily selected. For items not available in this list, manual entry of the name of the product, form, strength and original pack quantity will be required. The database and data collection process have been piloted with three RUM bins at the Queensland incineration plant and a number of modifications were implemented. The Access® database has been loaded onto laptop computers for data entry in real time at each incineration site.

**Table 2 Tab2:** Variables to be included in RUM audit and post-audit analyses

Characteristics of RUM bins	Source of container (state or territory)
	Container weight
	Percentage filled
Content of RUM bins	Medicine characteristics
	Brand name
	Generic name
	Manufacturer
	Medicine schedule (i.e. unscheduled, S2, S3, S4 or S8)
	Therapeutic category (PBS code)
	Medicine dose
	Form of medicine
	Whether medicine is PBS subsidised or private
	Whether medicine is expired
	Packaging of medicine included
	Evidence of attempted destruction for S8 medicines
	Presence of inappropriate items (e.g. sharps, rubbish)
	Complementary and alternative medicines
	Medicine in a sample package

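### An empty bottle alone counts as evidence that a Schedule 8 medicine was destroyed, so this Table 2 variable may be overstated by an amount the article does not allow to be computed

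*Protocol article*

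**What the plan says.** The rule stands in the Protocol article, Stage One, *Bin and contents inspection*. An S8 item is flagged in the database "together with any evidence of destruction (i.e. cut and empty foil strip or an empty bottle". A foil strip has to be both cut and emptied, whereas a bottle only has to be empty.

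The rule feeds a variable that Table 2 (*Data collection and training*) labels "Evidence of attempted destruction for S8 medicines". The table speaks of attempted destruction and the inspection text of destruction.

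Other fields bear on the same item. Table 2 lists "Evidence of medicine use" and "Quantity returned". The text of *Data collection and training* explains the former as whether the pack was opened or full. Empty containers are foreseen: "For liquids, the percentage returned is estimated (empty = 0" percent. Unit-dose items are counted individually.

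The first Stage One objective in *Study design overview* is "To quantitatively describe the amount and types of medicines returned to pharmacies using a statistically valid sample of returned RUM bins"; the second concerns PBS-subsidised waste. The Stage One *Data analysis* section says that "audit data will be cleaned in preparation for visualisation and descriptive data analyses".

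**The concern.** A data collector who applies the rule exactly as written will record a bottle that the patient finished as showing evidence of destruction. This is a fault of the definition and not of its execution, so training to the rule, re-inspection of bins and checks of data entry would not remove it. They test whether the rule was followed, not whether it measures what its label says.

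At stake is the meaning of one descriptive variable. Any reported share of S8 items with evidence of destruction would mix consumed with destroyed medicines in unknown proportions. Because audited bins are on their way to incineration, a distinction not recorded at inspection is unlikely to be recoverable later.

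**Working it through.** The article gives no figure for S8 destruction, so there is none to reproduce. The sample size of 373 bins does not enter this point.

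**Step 1. Can the recorded fields tell the two cases apart?** Take two S8 bottles, one emptied by use and one whose contents were destroyed and removed.

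| Field | Emptied by use | Contents destroyed and removed |
|---|---|---|
| Quantity returned | 0 | 0 |
| Evidence of use (opened or full pack) | opened | opened |
| Evidence of destruction under the inspection rule | yes | yes |

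The rows are identical. Quantity dispensed does not help, since it describes the supply and not the fate of the contents. For strips the rule asks for a physical sign (the cut) in addition to emptiness; for bottles it asks for none.

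**Step 2. Direction of this error.** Let *d* be the share of all S8 items truly destroyed, and *u* the share of the remaining items that are bottles emptied by use. If every true destruction is recorded and nothing else is misclassified:

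recorded share = *d* + (1 − *d*) × *u*, so excess = (1 − *d*) × *u*.

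The excess is zero when *u* = 0 and never negative. Taken alone, the empty-bottle error can only push the share upward.

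**Step 3. Illustration over assumed values.** Neither *d* nor *u* is in the article; both are assumptions chosen to show sensitivity.

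| *d* | *u* = 5% | *u* = 10% | *u* = 20% | *u* = 40% |
|---|---|---|---|---|
| 10% | 14.5% | 19% | 28% | 46% |
| 30% | 33.5% | 37% | 44% | 58% |
| 50% | 52.5% | 55% | 60% | 70% |

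For example, 0.30 + 0.70 × 0.10 = 0.37. Over this grid the excess runs from 0.50 × 0.05 = 2.5 percentage points to 0.90 × 0.40 = 36 points. A range this wide shows that the size depends on the assumed *u*; it is not an estimate.

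**Step 4. Net direction.** If a share *m* of true destructions were missed, for instance contents still present but visibly altered, the net error would be (1 − *d*) × *u* − *d* × *m*. With *d* = 30% and *u* = 10% the upward part is 7 points, and it is cancelled when *m* = 0.07 / 0.30 = 23%. Whether any are missed depends on how strictly the rule is read, so even the sign of the net error is not fixed by the article.

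**The case against.** **The variable is minor.** This stands. S8 destruction is one of many descriptive Table 2 items. A reader might infer that the audit has an S8 compliance outcome, but the two Stage One objectives do not mention one, and the *Data analysis* section states no compliance rate, denominator or test.

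**Overstatement is not shown.** This stands too. A reader might infer that the result is inflated as a matter of fact. That depends on how many S8 bottles emptied by use reach the bins, which the article does not say, and Step 4 leaves the net direction open. Only the possibility is established.

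**The definition may not be closed.** The same section uses the abbreviation *i.e.* before a list of unit-dose forms that ends in *etc.*, so it is not used strictly, and altered contents could be covered by the general wording about any evidence of destruction. A firm claim that such items are missed is therefore not supported. This does not help with bottles: an empty bottle is named expressly as qualifying, however the list is read.

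**Operating detail may sit elsewhere.** The article says that a data collection protocol and training tools exist and can be requested. They may refine the rule. The published rule is nevertheless a stated criterion and not an omitted detail, and as stated it misclassifies.

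**An analyst could isolate zero-quantity S8 bottles afterwards.** Partly so: form, packaging and quantity might allow a report with and without them. But whether the bottle showed signs of tampering would not have been recorded.

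**Excluded bins.** A reader might also infer that destroyed S8 contents are lost through the exclusion of bins with "unknown liquid or powder waste". Nothing in the article says that destroyed contents take that form. The exclusion is a safety rule, and the instruction to reseal a bin with inappropriate items at once leaves no room for recording S8 labels first.

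**Conclusion.** The point holds in a limited form. Under the published rule an empty S8 bottle is by itself evidence of destruction, and no other field shown distinguishes use from destruction. The Table 2 variable may therefore be overstated. The amount cannot be derived from the article, and the percentages above are illustrations on assumed values. The conclusion rests on two assumptions: that collectors apply the rule as published, and that some S8 bottles emptied by use reach the bins. The second is plausible, since the plan provides a code for empty liquid containers, but it is not quantified. The Stage One objectives, the PBS wastage estimate and the number of bins are not affected. The matter is modest, but it concerns the validity of something the audit chose to record, so it is worth correcting before collection starts.

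**What to change.** In the Access database, give the S8 destruction field a separate option for an empty bottle with no sign of tampering, labelled *empty, cause undetermined*. Keep it distinct from positive signs: a strip cut and emptied, or contents present but visibly altered. Report the share of S8 items with evidence of destruction twice, with and without the undetermined category.

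Present the two figures as a sensitivity range and not as strict bounds. A cut and emptied strip can also result from ordinary use, and some undetermined bottles may have been emptied in order to destroy the contents.

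Use one term in both places, so that the inspection text and Table 2 both refer either to destruction or to attempted destruction, with the same list of qualifying signs.

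The cost is one extra drop-down option, one line in the training material, and a result given as a range instead of a single figure. The sample size does not change.
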